### Data collection

#### Outcome data

Clinical outcome data will be extracted from patient records maintained by the community health teams and the clinic. Outcome variables that will be retrospectively extracted from the child contact file include presence of symptoms (binary, yes/no will be asked for each symptom), gastric aspirate/Xpert/culture results (if applicable), chest X-ray results (if applicable), the TPT or active TB treatment initiation date, the TPT regimen, planned and actual dates of all follow-up visits, TPT completion date, and reasons for early discontinuation including patient preference, pregnancy (adolescents), and severe disease including malaria or side effects including flu-like illness, hypersensitivity reactions, hepatotoxicity, and peripheral neuropathy (if applicable). We will collect information regarding the location of child contact screening, TPT initiation, and all subsequent follow-up visits. We recognize these outcomes are dependent on clinic staff compliance with study tools. Periodic monitoring of study tools will be performed, and additional training will be provided if study tools are not being used optimally.

#### Missing data

Our sample size calculations have adjusted for potential refusals or losses to follow-up, and thus we expect to achieve the same level of power if up to 20% of diagnosed TB patients either refuse to participate or are enrolled and do not complete the study. We anticipate that these losses will occur completely at random and thus inference based on remaining participants will be valid. Data will be abstracted from clinic records, and we expect some missing data. We will work with study staff to investigate any missing data related to study endpoints to determine if there is systematic missingness. If appropriate, suitable imputation methods will be applied for missing covariate data.

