### Objectives and endpoints

The primary objective of this study is to determine the effectiveness of home-based contact management, including TPT initiation and follow-up, using community-based healthcare workers to increase TPT initiation as compared to facility-based contact management. The primary endpoint is the cluster-level ratio of the number of household child contacts less than 15 years of age in Ethiopia and less than 5 years of age in South Africa initiated on TPT (3HP, 3RH, or 6H) per index patient, comparing the intervention to the control arm (Table 1). Because we anticipate heterogeneity in the epidemiology of TB and potential differences in the response to the intervention between countries, the primary outcome will be assessed across countries and within countries.

**Table 1 Tab1:** Primary and secondary outcomes for the CHIP-TB trial

**Primary outcome**	**Outcome description**	
TPT initiation among child contacts	The cluster-level ratio of the number of household child contacts less than 15 years of age in Ethiopia and less than 5 years of age in South Africa initiated on TPT per index patient, comparing the intervention to the control arm	
**Secondary outcome**	**Outcome description**	
Child contact identification	The cluster-level ratio of the number of household child contacts less than 15 years of age in Ethiopia and less than 5 years of age in South Africa identified per index patient	
Continuum of care	The cluster-level proportions of estimated child contacts who progress through each stage of the pediatric TB prevention continuum of care (identification, screening, initiation, and completion) overall and by age, by TPT regimen, and by country. *estimated child contacts will be calculated using DHS data	
Treatment completion (as defined by WHO TPT Handbook)	• Proportion of children initiated on TPT who successfully completed TPT • Proportion of children initiated on TPT who were lost to follow-up • Proportion of children initiated on TPT with incident TB (treatment failure) • Proportion of children initiated on TPT who died • Proportion of children initiated on TPT who discontinued TPT due to: toxicity, drug-drug interaction, severe illness (e.g., malaria), pregnancy, or family preference *Treatment completion was defined as 11 doses in 16 weeks for 3HP and 68 doses in 4 months for 3RH [19].	
**Implementation outcome**	**Quantitative assessment**	**Qualitative assessment**

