Acceptability of home-based contact management to all stakeholders (CG, HEW, TBF, PM)	• Proportion of identified households who agree to a home visit • Proportion declining HIV testing (South Africa only) • Proportion of children HIV tested by the community health team • Proportion of newly diagnosed HIV-positive children who are referred to the clinic for ART initiation	• Individual in-depth interviews (CG, HEW, TBF, PM)
**Fidelity** to the home-based contact management strategy	• Proportion of children initiated on the correct TPT regimen • Proportion of children initiated on the correct TPT dose	• Individual in-depth interviews (CG, HEW, TBF, PM)
**Feasibility** of home visits for CGs and community-based health teams	• Average number household visit attempts per household • Mean and median duration of each household visit • Proportion of index patients who refuse to provide an address or who provide an invalid/incorrect address	• Individual in-depth interviews (CG, HEW, TBF, PM)
**Cost and cost effectiveness**	• Mean difference in total patient and health system costs between the intervention and control arms • Incremental cost-effectiveness ratio (ICER) where effectiveness is modeled as the number of disability adjusted life years (DLYs) averted by the intervention in comparison with the standard of care.	• Structured interviews to assess implementation costs • Time and Motion observations of TB preventive care

Stakeholders: *CG* Caregiver, *HEW* Health extension worker, *TBF* TB focal persons, *PM* Program manager

The secondary objectives of the study are to evaluate: (1) the TPT continuum of care by country, TPT regimen (3RH and 3HP), and age (< 5 and 5–14 years); (2) acceptability, feasibility, and fidelity of home-based contact management and HIV preventive services in each setting; (3) TPT treatment outcomes, including tolerability and reported adherence; and (4) the cost-effectiveness of home-based versus facility-based child contact management (Table 1).

Data will be collected on staffing changes within the TB clinic and community health teams and stockouts of TPT medications, pyridoxine, and other supplies needed for pediatric contact management (specimen collection, file and registers, etc.), to understand trends in the data.

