### Study population

The study will attempt to enroll all close child contacts of individuals diagnosed and treated for infectious drug-sensitive TB in the study clinics. Good Clinical Practice (GCP)-trained study and clinic staff will enroll participants. Eligibility criteria for index patients and child contacts are pragmatically designed to align with the Ethiopian and South African National Guidelines regarding TPT eligibility. We will enroll index participants with pulmonary TB disease who (1) are 18 years and older, (2) attend a study clinic for TB care and live in the catchment area of that clinic, (3) are willing to have a home visit and disclose their TB diagnosis to household members, and (4) who provide informed consent. In South Africa, all index patients will need bacteriologic confirmation of pulmonary TB disease by smear, Xpert, and/or liquid mycobacterial culture. In Ethiopia, index patients may have bacteriologic confirmation or clinical diagnosis. Index patients in both countries will be excluded if there is evidence of rifampin and/or isoniazid resistance on Xpert or drug sensitivity testing from isolates identified on culture (late exclusion) or if the household has more than one index patient and whose child contacts have already participated in the study. Child contacts will be enrolled if (1) they are less than 15 years of age in Ethiopia or less than 5 years of age in South Africa, (2) they are a close contact of the index patient, and (3) their parent or legal guardian is willing to provide informed consent. Additionally, in Ethiopia, children 12 years and older must be willing to provide assent. Child contacts in both countries will be excluded if any index patient in their household has drug-resistant TB by either Xpert or drug sensitivity testing. Eligibility criteria will be adapted as country guidelines are updated.

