### Sample size considerations

We considered sample size estimation for the South Africa and Ethiopia sites separately because of the differences in TB epidemiology in the two countries. Sample size calculations were based on the primary outcome which is the clinic-level number of child contacts under age 15 years (Ethiopia) or under 5 years (South Africa) initiating TPT per index patient, compared between the two study arms. We expect there to be a harmonic mean of 51 and 32 diagnosed TB patients per clinic during the study period, in South Africa and Ethiopia respectively. We also expect 20% refusals, withdrawals, or loss to follow-up leading to an average of 40 and 26 TB patients, as reported by the respective TB programs. An estimate of the coefficient of variation (CV) was obtained from a previous contact tracing study in South Africa which was 0.35 [6]. We assumed a similar amount of between-cluster variability in Ethiopia, and we also evaluated how the required sample size changed if we considered a slightly higher CV of 0.4. Prior household-based contact tracing studies and 2016 DHS data showed that households of index TB patients in South Africa and Ethiopia, respectively, have 1.8 and 2.1 children under the age of 15, and we expect that 30% would initiate TPT under the standard of care [6, 29–32]. We hypothesize that the intervention would double the number of children per TB patient initiated on TPT — from 0.5 (=1.8×0.3) to 1 in South Africa, and 0.6 (=2.1×0.3) to 1.2 in Ethiopia. A total of 18 (9 per arm) clinics in each country would be required to detect this effect with 80% power at a 5% level of significance assuming a CV of 0.35. A larger CV of 0.4 would require 20 and 22 clinics in South Africa and Ethiopia, respectively.

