### Statistical analysis

#### Primary and secondary outcome analyses

Summary statistics of the enrolled index patients will be presented stratified by arm and study site. Analysis of the primary outcome of the number of child contacts less than of 15 years of age in Ethiopia and less than 5 years of age in South Africa who initiate TPT per index patient diagnosed will be stratified by country. Cluster-level ratios will be compared between arms using an unpaired t-test which has been shown to be robust for a relatively small number of clusters [24]. The ratio of the study arm mean ratios and the corresponding 95% confidence interval will be calculated. A log-transformation of the cluster-level ratios will be applied before applying the *t*-test if the outcomes are highly skewed. If the number of index patients varies substantially between clinics, weighted (by clinic size) mean ratios will be used. If the sample size allows, we will compare the numbers of children started on TPT between arms stratified by TPT regimen (3HP vs 3RH) and children’s age groups (^3^5 vs <5 for Ethiopia).

Secondary outcomes to be compared between arms will be the number of child contacts identified (using index patient’s clinic-based contact tracing report, the child contact management file, and the community-level file maintained by the community health team) per index patient, and the proportions of these who are screened, initiated on TPT and who complete TPT. As done for the primary outcome, cluster-level summaries for secondary outcomes will also be compared between arms. Count outcomes will be compared using Poisson regression, and cluster-level proportions (after a log-transformation, if necessary) will be compared using a *t*-test.

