#### Statistical plan for protocol non-adherence

The primary analysis will be intention to treat. We will explore who did and did not receive TPT initiation in the home vs clinic, as per their assigned arm. We will summarize such deviations. There are no planned per protocol or as treated analyses.

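### The primary ratio is per diagnosed index patient in one section and per remaining participant in others, and the completely-at-random assumption meant to bridge the two is not supported

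*Protocol article*

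**What the plan says.** All references are to the protocol article.

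- **Objectives and endpoints** counts child contacts "initiated on TPT (3HP, 3RH, or 6H) per index patient, comparing the intervention to the control arm". It does not say whether the index patients are those diagnosed or those enrolled.
- **Primary and secondary outcome analyses** is specific. It counts children "who initiate TPT per index patient diagnosed will be stratified by country".
- **Study population** enrols index patients only if they give consent and "are willing to have a home visit and disclose their TB diagnosis to household members". The criterion is written for both arms.
- **Sample size considerations** starts from 51 (South Africa) and 32 (Ethiopia) diagnosed patients per clinic and then reduces them: "We also expect 20% refusals, withdrawals, or loss to follow-up leading to an average of 40 and 26 TB patients".
- **Missing data** says power will hold "if up to 20% of diagnosed TB patients either refuse to participate or are enrolled and do not complete the study", and continues: "We anticipate that these losses will occur completely at random and thus inference based on remaining participants will be valid".
- **Statistical plan for protocol non-adherence** states: "The primary analysis will be intention to treat".
- **Table 1** lists among the acceptability measures "Proportion of identified households who agree to a home visit", and among the feasibility measures the share of index patients who give no address or a wrong one.

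**The concern.** Diagnosed patients and remaining participants are different denominators, and the article uses both for the same primary ratio. They would give the same answer on average if the people left out were a random subset, which is what Missing data asserts. Three features of the design argue against that:

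- **Allocation is known first.** Clinics were told their arm before the study began in either country, and patients, providers and analysts are all unmasked. Each index patient's decision to take part follows allocation.
- **The entry question means different things in the two arms.** In the intervention arm, agreeing to a home visit is agreeing to the intervention. In the control arm, care takes place at the facility and the same question is largely hypothetical.
- **Refusal is treated as an outcome.** The trial measures home-visit agreement as acceptability and plans to summarise reasons for refusal in the intervention arm. The same refusals cannot also be presumed to be random noise in the primary analysis.

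At stake is the primary estimate. A family that will not accept a visit is one the home strategy fails to reach. If such families leave the home-arm denominator while comparable control families stay in, or would have brought their children to the clinic anyway, the ratio answers a question about willing households and not the clinic-level question the trial poses.

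**Working it through.** **1. Which denominator the planning figures use.** Applying the 20% loss to the diagnosed counts: 51 × 0.8 = 40.8 (stated as 40) and 32 × 0.8 = 25.6 (stated as 26). The planned denominator is therefore the patients remaining after refusals and losses, not those diagnosed.

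**2. Bias from leaving people out.** Let *d* be the share of diagnosed index patients left out and *q* the initiation rate among those left out relative to participants in the same arm (*h* = home, *c* = control). The rate per diagnosed patient equals the participant rate times (1 − *d* + *dq*). The reported ratio of arm means divided by the ratio per diagnosed patient is

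B = (1 − d_c + d_c·q_c) / (1 − d_h + d_h·q_h).

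The 20% comes from the article. The split by arm and every *q* are assumptions, because the article gives neither.

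| d_h | d_c | q_h | q_c | B |
|---|---|---|---|---|
| 0.2 | 0.2 | equal | equal | 1.00 |
| 0.2 | 0.2 | 0 | 1 | 1.0/0.8 = 1.25 |
| 0.2 | 0.2 | 0 | 0.5 | 0.9/0.8 = 1.125 |
| 0.2 | 0.2 | 0.5 | 1 | 1.0/0.9 = 1.11 |
| 0.2 | 0.2 | 0.5 | 0 | 0.8/0.9 = 0.89 |
| 0.2 | 0.2 | 1 | 0 | 0.8/1.0 = 0.80 |
| 0.2 | 0 | 0 | any | 1.0/0.8 = 1.25 |
| 0.2 | 0.1 | 0 | 0 | 0.9/0.8 = 1.125 |
| 0.1 | 0.2 | 0 | 0 | 0.8/0.9 = 0.89 |

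The fourth row is the case where home-arm refusers' children still reach the clinic and start at the planned control rate (0.5 against 1.0 among participants in South Africa, so q_h = 0.5), and control refusers behave like control participants.

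**3. Against the planned effect.** The article plans a ratio of 1.0/0.5 = 2.0 in South Africa and 1.2/0.6 = 2.0 in Ethiopia. If 2.0 were observed among remaining participants, the ratio per diagnosed patient would be 2.0/1.25 = 1.6, 2.0/1.125 = 1.78, 2.0/1.00 = 2.0 or 2.0/0.889 = 2.25, depending on the row.

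**4. Effect on the test.** Gamma-Poisson clinic counts were simulated with 9 clinics per arm, between-clinic CV 0.35, 40 or 26 index patients per clinic, an unpaired t-test and 40,000 replicates. There was no true effect per diagnosed patient, and the home-arm rate was multiplied by B. Two-sided rejection at the 5% level:

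| B | South Africa | Ethiopia |
|---|---|---|
| 1.00 | 4.8% | 4.8% |
| 1.125 | 8.6% | 8.6% |
| 1.25 | 18.9% | 17.7% |

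**The case against.** The strongest reply is that the removal is matched. Home-visit willingness, disclosure and consent are required of every index patient, and the 20% is not split by arm. If refusal and refusers' behaviour are alike in the two arms, B is exactly 1.00. It can also fall below 1. This stands. A reader might infer that the plan biases the ratio toward the home arm as a matter of fact, or that a reported 2.0 is really 1.6. The article supports neither reading. The 1.6 requires that the whole 20% be people whose children never start TPT in the home arm, although the figure pools refusals, withdrawals and losses, and that control non-participants start as often as participants.

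A reader might also infer that acceptability will be computed among the enrolled and so approach 100%. Nothing says so: Table 1 refers to identified households, and the analysis section summarises visit refusals among those approached.

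Nor does leaving out non-enrolled patients contradict intention to treat as the article uses the term. That section is about analysing by assigned arm when TPT is started in the other setting. The narrower point holds: Missing data counts enrolled patients who do not complete among the losses and rests inference on the remainder. If they leave the primary ratio, that does not fit an intention-to-treat analysis, and TPT initiation can be abstracted without later completion.

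Finally, Missing data promises to investigate systematic missingness in endpoint data. That concerns records being abstracted, and imputation is offered only for covariates. Neither recovers patients who never enrolled.

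**Conclusion.** Two findings are firm. The primary denominator is inconsistent between sections, and the statement that losses are completely at random is not supported by a design in which unmasked enrolment follows allocation and the entry criterion is acceptance of the intervention's own component.

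Direction and size are conditional. Exclusion can bias the ratio. A shift toward the home arm is the more plausible direction, because refusing the visit defeats home delivery whereas a similar control family can still attend the clinic. At 20% loss in both arms the factor is about 0.89 to 1.25 in the main scenarios. The full span, with refusers' initiation anywhere from none to the participant rate in each arm, is 0.80 to 1.25. It is 1.00 if refusers behave alike. At the upper end, and with no true effect, the false-positive rate would be about 18 to 19%. Because this decides what the primary estimate means, it should be settled before the data are analysed.

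**What to change.** Enrolment had begun in both countries when the article was written, so the change belongs in the analysis and data abstraction.

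1. State one primary denominator: all index patients in the clinic TB register during the study window who meet the clinical criteria, in both arms. Keep refusers and enrolled non-completers in it.
2. Take the numerator from aggregate routine TPT and contact records for the same window, where ethics approval allows. This matters. If only enrolled children are counted, changing the denominator corrects for unequal loss between arms but not for refusers behaving differently between arms.
3. Report refusals and non-enrolment by arm, and present the per-enrolled ratio as secondary.
4. Replace the completely-at-random sentence with a two-sided sensitivity analysis that uses the observed non-enrolment in each arm and varies refusers' initiation from none to the participant rate separately in each arm.

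**Cost.** Modest extra register abstraction, and possibly a smaller effect estimate. TB notification counts by clinic were available for randomisation, and a standard contact form runs in both arms. Whether that form covers non-participants' children, and whether aggregate counts for them are permitted, cannot be told from the article. Where they cannot be counted, the sensitivity analysis carries the weight.

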#### Costing and time-and-motion data

Costs will be measured prospectively from study data from the societal perspective and will include costs related to both health systems and patients. Health systems costs will be captured using an “ingredients” approach through a combination of budgetary review, key informant interviews, direct observation of healthcare workers (time-and-motion observations), and time-stamped case report forms [33]. Health systems costs will include labor, training, transport, infrastructure, supplies/consumables, and other administrative/support costs. Patient costs will include transport, lost wages, clinic fees (if applicable), food, and child/family care. Costs will be measured on up to 400 index households (up to 100 interviews per arm per country). Patient-level costs will be measured through a standardized questionnaire completed by the caregiver responsible for enrolled children. The questionnaire will use the “Tuberculosis patient cost surveys: a handbook” as a guide and will also include the global multidimensional poverty index [34, 35].

#### Qualitative data

Data were collected by trained study staff before and will be collected after the trial through in-depth interviews in English, Amharic, Afan Oromo, isiZulu, and Sepedi. Participants included and will include program managers, providers, community health team members, and child caregivers. Interviews will be transcribed, translated, and coded by experienced qualitative researchers. The baseline interview focused on perceptions of the planned intervention including barriers and facilitators to its implementation. Post-trial interviews will focus on the intervention arm and will assess each stakeholder groups’ perception of the intervention’s acceptability and feasibility along with lessons learned. All participants provided or will be asked to provide informed consent for participation in each interview. Confidentiality will be maintained by not using names of people, clinics, or locations within the interview and eliminating specified people or places during transcription. We plan to use thematic analysis guided by the Consolidated Framework for Implementation Research (CFIR) [36].

